#### Analysis of quantitative data

Quantitative data will be analyzed via both multilevel models and at separate levels: primary care organization, staff and patients. In the initial analyses, all primary care centers that have implemented PCBH will be considered intervention centers; i.e., analyses will be performed according to the ITT principle. Since features of the implementation might differ between centers, per-protocol analyses will also be conducted based on centers with high fidelity to PCBH core components. Differences between sexes will be investigated.

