### Implementation of the model

There is a regional decision that PCBH should be implemented in the whole primary care in RÖ in the south-east region of Sweden, and the research group is working closely with the assigned regional implementation team, which consists of psychologists with special training in PCBH.

The implementation process will be carried out according to the Swedish Public Health Agency’s “Checklist for implementation with quality” [26]. 1) Initial assessment of needs and resources; 2) structure for implementation; 3) actual implementation; and 4) learn and improve. For each primary health care center, an initial assessment of needs and resources take place, followed by an individually tailored structure for implementation. When implementation starts, all medical staff receive a PCBH education for 1–4 days depending on the profession (e.g., 4 days: staff categories who will take on the role of on-site behavioral health consultants, typically psychologists and psychotherapists; 2 days: nurses; 1 day: physicians). Thereafter, tutoring sessions per profession are being carried out approximately once/month, more often if needed, to promote retention of the PCBH model. The active implementation period for each intervention center is approximately 12 months, during which scheduled lectures and workshops, continuous on-demand support, materials and instructions are provided by the implementation team. Thereafter, further support for maintenance will be offered by the implementation group for at least 24 months according to the needs of each center. All the implementation activities are endorsed and funded by RÖ. See also Fig. 1: SPIRIT flow diagram.

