### Participants

#### Primary care center recruitment

Four pilot primary care centers have already been enrolled in the project, to test the protocol. After this pilot enrollment and adjustments of the implementation procedure, the protocol was adjusted to the final version. Following the pilot implementation of PCBH, a total of 24 primary care centers in RÖ will be enrolled in the research project (representing a total of 70% of all centers in this region). According to a staggered timetable, eight centers will be included in Year 1, eight in Year 2 and eight in Year 3, for a total of 24 centers over a three-year period. These 24 primary care centers in RÖ will be matched with 48 control centers from adjacent county councils in Jönköping, Kalmar and Örebro. Matching will be based on the number of listed patients, number of employees, number of behavioral health consultants and physicians and characteristics of the catchment area (CNI and ACG). A similar cluster-based approach has previously been used in research conducted at Linköping University [31].

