#### Statistical considerations

Quantitative data will be analyzed in both multilevel models and on separate levels: organization, staff and patients. Data will be collected from all centers who have initiated use of the PCBH model and in the initial analyses, all primary care centers will be considered intervention centers; i.e., analyses will be performed according to the intention to treat (ITT) principle. In addition, since features of the implementation might differ between centers, analyses will also be conducted based on centers with the highest fidelity to PCBH core components. Organization characteristics of the included primary care centers will also be collected and accounted for in the analyses, i.e., number of employees, number of behavioral health consultants and physicians, number of listed patients, characteristics of the catchment area, CNI and ACG. Furthermore, the PCBH model can be expected to require local adjustments for each primary care center. These adjustments will be carefully monitored for each participating center, and their impact on outcomes will be analyzed. In addition, data about mental health interventions (e.g., CBT) and the format of delivery (e.g., internet-based or self-help materials) will also be documented and addressed in the analyses.

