#### Sample size

Approximately 3% of all patients in primary care receive an intervention by a behavioral health consultant [6, 13]. We hypothesize that this number will be at least 50% higher in the intervention group compared to the control group. A sample size based on a 50% increase, a power of 0.8 and a significance level of 0.05 yields a minimum of 1983 participants per group. Since we are using a design where heterogeneity of the populations and primary care centers probably will reduce the likelihood to detect meaningful changes, it is reasonable to double the number of participants to 3966 individuals per group. One of the pilot primary care centers has 14,841 listed patients. A study regarding Swedish primary care showed that approximately 66% of the population receives care annually at a primary care center [5]. It can thus be estimated that 9,795 (14,841 × 0.66) individual patients receive care annually at this center. If we assume that 3% [6, 13] of these patients receive a behavioral health consultant intervention, approximately 294 (9,795 × 0.03) patients annually receive a PCBH-based intervention. After the implementation of the PCBH delivery model, we estimate that this number will increase to 441 individual patients per year for one single primary care center (i.e., a 50% increase in the intervention group: 294 × 1,5 = 441). Since the project will involve 24 primary care centers, the requested sample size of at least 3966 individuals will not pose any difficulties, even considering that the number of listed patients among these centers ranges from approximately 4,500 to 21,500 listed patients (in December 2022). It should be noted that it is difficult to estimate the power of cluster studies because there can be heterogeneity within and between clusters.

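### The analysis labelled ITT picks its intervention centres by whether they initiated or implemented PCBH, not by enrolment or scheduled step, and the two wordings disagree

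*Protocol article*

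**What the plan says.** Four places in the protocol article bear on which centres form the intervention group.

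- *Primary care center recruitment* fixes the enrolled set, "a total of 24 primary care centers in RÖ will be enrolled in the research project", and the schedule, "eight centers will be included in Year 1, eight in Year 2 and eight in Year 3". These centres are matched with 48 controls.
- *Statistical considerations* says "Data will be collected from all centers who have initiated use of the PCBH model". It then labels the main analysis as follows: "in the initial analyses, all primary care centers will be considered intervention centers; i.e., analyses will be performed according to the intention to treat (ITT)".
- *Analysis of quantitative data* says that "all primary care centers that have implemented PCBH will be considered intervention centers; i.e., analyses will be performed according to the ITT principle". The only contrast it offers is that "per-protocol analyses will also be conducted based on centers with high fidelity to PCBH core components".
- *Implementation of the model* says "The active implementation period for each intervention center is approximately 12 months", so starting and having implemented can be a year apart.

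Neither analysis section refers to enrolment or to the scheduled step, and neither says how a centre that starts late, or never, is classified. The RQ1 section likewise sets its before and after periods around implementation, not around the scheduled step.

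**The concern.** In a staggered roll-out, analysis by intention means that a centre counts as exposed from its planned step, whatever it then does. Here, membership of the intervention group depends on something that happens, or fails to happen, after enrolment. The label ITT then means only that fidelity is ignored once PCBH has been started or put in place.

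The trial is pragmatic and follows a regional decision to introduce PCBH, so late, stalled or failed starts are part of the answer it seeks. Whether a centre gets going plausibly depends on its staffing, leadership and workload, which may also affect access, sick leave and referrals. The pilot shows how far centres can differ: the increase in patients treated ranged from 11% to 194%, and waiting lists disappeared in three of four centres. With 24 intervention centres, the classification of a few could move the main estimate. If the set is left open until results are known, its membership could also be influenced by which centres succeeded.

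**Working it through.** **1. The three definitions side by side**

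| Centre | By enrolment and schedule | Initiated wording | Implemented wording |
|---|---|---|---|
| Starts on time and completes | Intervention | Intervention | Intervention |
| Starts late | Intervention from planned step | Intervention once started; gap not addressed | Intervention once implemented; gap not addressed |
| Starts, then stalls | Intervention | Intervention | May not count |
| Never starts | Intervention | May not count | May not count |

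The wordings agree for a centre that completes on time. They part for a stalled centre, and both part from the enrolled set for a centre that never starts.

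**2. The plan's own figure**

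The rates used below come from *Sample size*: "Approximately 3% of all patients in primary care receive an intervention by a behavioral health consultant", with a hypothesised 50% increase, so p1 = 0.03 and p2 = 0.045. With pooled variance,

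n = [z(α)·√(2·p̄·(1−p̄)) + z(power)·√(p1(1−p1) + p2(1−p2))]² / (p2−p1)², with p̄ = 0.0375.

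A one-sided 5% test with power 0.80 gives [1.645 × 0.2687 + 0.842 × 0.2685]² / 0.015² = 1983 per group, as stated. A two-sided test gives 2518. This confirms the rates; the present point does not rest on it.

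**3. What the definition could do to the estimate (illustration)**

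Assumptions: 24 equal-sized centres; k never implement and stay at 3%; the others reach 4.5%; controls are at 3%. The documents give no value for k.

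Rate by schedule = [(24−k) × 4.5% + k × 3%] / 24. The as-implemented analysis shows 4.5% against 3%, a rate ratio of 1.50, whatever k is. The overstatement of the difference is 24/(24−k).

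| k | Rate by schedule | Rate ratio by schedule | Difference overstated by |
|---|---|---|---|
| 2 | 4.375% | 1.458 | 24/22 = 1.09 |
| 4 | 4.250% | 1.417 | 24/20 = 1.20 |
| 6 | 4.125% | 1.375 | 24/18 = 1.33 |
| 8 | 4.000% | 1.333 | 24/16 = 1.50 |

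Under these assumptions it makes no difference whether the k centres are dropped or counted as unexposed, because they sit at the control rate.

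**4. Is the direction certain?**

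Suppose PCBH has no effect, the 24 centres average 3%, and 6 with rate b are left out. The rest average (24 × 3% − 6b)/18.

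- b = 2.0%: 3.33%, ratio 1.11
- b = 2.5%: 3.17%, ratio 1.06
- b = 3.5%: 2.83%, ratio 0.94
- b = 4.0%: 2.67%, ratio 0.89

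In this plain comparison without baseline adjustment, selection alone can push the estimate either way.

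**The case against.** A reader might infer that the plan drops centres that are late, stall or never start, and that the main effect is therefore biased upward. The documents do not support that reading.

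- Neither analysis section states an exclusion. Taken as a complete rule, the sentence on data collection would also shut out the 48 controls, which the design needs. *Ethical considerations* has registry data retrieved from eligible patients at any participating centre, and the RQ8 section collects implementation costs for each of the 24 centres.
- Under the initiated wording, a centre that starts and stalls stays in. ITT is contrasted only with a high-fidelity subset, so the evident aim is to keep centres regardless of how well they perform. That is a real part of intention to treat.
- The direction is open, as step 4 shows. Outcomes for RQ1 are measured before and after implementation, and organisational characteristics, staffing among them, are to be accounted for. Both could reduce bias from selection.
- The roll-out is a regional decision, regionally funded and supported by a dedicated team, so non-starters may be few.
- The article gives inclusion by year only and describes no random order. Analysis by schedule would remove selection on starting; it would not supply the protection of randomisation.
- How matched controls are handled in the high-fidelity analysis is detail that an article may leave to the analysis plan.

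All of this stands and limits the point. It does not turn either stated condition into intention to treat, and it does not reconcile the two. Because the article itself states and labels the rule, twice, this is not a detail left to an unseen document.

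**Conclusion.** The point holds as a fault of definition. The set called ITT rests on an event after enrolment, is worded in two incompatible ways, and does not match the 24 enrolled centres. Followed literally, it yields an as-implemented estimate under the wrong name.

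A bias is possible but not demonstrated. The 9% to 50% range requires that PCBH works, that non-implementing centres gain nothing, that centres are of equal size, and that 2 to 8 of 24 do not implement. All but the size of the working effect, which is the plan's own hypothesis, are assumptions made here. The correction should be made before results are known.

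**What to change.** Define the main analysis set as all 24 enrolled centres plus the 48 controls, with exposure assigned by each centre's scheduled inclusion step (Year 1, 2 or 3), whatever its actual start or fidelity. Label the analysis by actual start as as-implemented, and treat it and the high-fidelity analysis as secondary. Use the same definition in *Statistical considerations* and *Analysis of quantitative data*, and state how a late or non-starting centre is handled.

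The cost is mostly wording, plus keeping the planned timetable as a data item. Most quantitative outcomes come from registries, so non-starters add little work; the staff questionnaires of RQ6 would need to be fielded there too.

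The price is a possibly diluted headline effect. Under the assumptions of step 3, with 3966 per group, a two-sided 5% test and clustering ignored, power falls from 94% with no non-starters to 90%, 85%, 77% and 68% with 2, 4, 6 and 8. These figures show the scale of dilution only; they are not a power statement for this clustered design.

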#### Analysis of qualitative data

Regarding the qualitative interview data (from patients and staff members), inductive content analysis according to Elo and Kyngäs will be employed [34]. Data analysis will include recommended steps, namely, open coding, coding sheets, grouping, categorization and abstraction. For all analyses, at least two researchers will be involved in the work to enable triangulation. In addition, NVivo or similar software will be used for data administration, sharing (between researchers) and analysis. Sex and gender considerations will be taken in account where relevant.

#### Ethical considerations

The study has been approved by the Swedish Ethical Review Authority (number 2020–05572), will be performed in accordance with the declaration of Helsinki, and is registered at clinicaltrials.gov (number NCT05633940). Health-related patient data can be considered sensitive data that warrant application to the ethical committee. Principal investigator [name] is responsible for reporting important protocol modifications in clinicaltrials.gov and other relevant parties.

For questionnaire and interview data, eligible participants will be provided with full written information about the study and the possibility of asking questions. Participants will be informed that participation is voluntary and that they can leave the study at any time point without providing an explanation, regardless of prior consent.

For registry data (medical records), informed consent will not be obtained. To increase the generalizability of the findings, registry data will be retrieved from all patients who have either been diagnosed with mental health problems or have received treatment for mental health problems at any of the participating primary care centers. Although the registry data will include sensitive data (e.g., diagnosis code, medication, comorbidity, sex and age), the Helsinki declaration states that there are situations when informed consent is not advised due to an unreasonable workload for participants. However, informed consent will be obtained from the medically responsible physician and manager at each participating center regarding the retrieval of registry data.

No human experiments will be conducted in this project. We estimate that there are minimal risks for participants (patients and staff) taking part in the project. Completing questionnaires regarding one’s health can be perceived as intrusive, and taking part in interviews can be perceived as uncomfortable. However, we believe that the benefits of this research outweigh the risks associated with participation. Indeed, mental health problems are a public health concern affecting a large proportion of the population both in Sweden and globally. This study has the potential to generate knowledge that is clinically relevant for primary care, benefiting a large proportion of the population suffering from mental health problems, thus contributing to the general good for the population and possibly providing better healthcare from a long-term perspective for the included patients. Regarding the included primary care staff, it is possible that psychosocial work environment problems will be identified, which offers the opportunity to improve the work environment for medical staff at both the intervention and control centers.

## Pilot study

The first 4 pilot centers that implemented PCHB have undergone some preliminary analyses to investigate feasibility of the project. The preliminary results are promising; in 3 of the 4 centers, the waiting lists to receive mental health care disappeared, and waiting times for visits for mental health problems decreased from 24.2 to 4.7 days (first visit) and from 22.5 to 6 days (revisits). At all the pilot centers, the number of patients who received care for mental health problems increased (a mean increase of 78%, range: 11–194%). The majority of the primary care staff at the pilot centers believed patients’ mental health care had improved and that their work had been facilitated by the implementation of PCBH, and 103 patients at the pilot centers reported being satisfied or very satisfied with the received care in a questionnaire on patient satisfaction.

## Discussion

This research project seeks to generate new knowledge about a real-world large-scale implementation and use of the PCBH model in routine primary care in Sweden. The project employs a multifaceted evaluation approach to enable an investigation of many different aspects of the PCBH model at the patient, staff and organization levels.

The project utilizes a Stepped-Wedge design, which is increasingly used in the evaluation of service delivery models [30] and was considered appropriate due to practical, logistical and resource constraints, which make it difficult to deliver the model en bloc. Stepped-wedge trials are considered more powerful than traditional parallel studies when clusters are relatively heterogeneous and/or large [31], which will likely be the case in this project. A pilot study was undertaken to determine whether the data collected to address the research questions would work as planned, demonstrating the feasibility of the research project.

An important ambition of the project is to address key knowledge gaps concerning PCBH. The planned studies have the potential to make numerous contributions to the research and practice concerning PCBH and primary care work for individuals with mental health problems. This is the first multicenter clinical trial with appropriate comparison groups. While there have been some small-scale studies of PCBH [7], there are only two published clinical trials [25, 26] and one study protocol of a pragmatic clinical trial [27] regarding PCBH. The study design will make it possible to assess many important results of the model at different levels.

The project emphasizes external validity and effectiveness rather than internal validity and efficacy. Hence, the focus is on real-world effects instead of effects under ideal, controlled conditions, which means that the project can provide a basis for decisions regarding further implementation and use of the model (or not) in other county councils. The project has the potential to generate clinically meaningful results that could be used for the future development of mental health care provision in primary care. Results will be published in international, peer-reviewed journals. Authorship will be based on the ICMJE criteria.

The research project is based on an interdisciplinary approach to stimulate an in-depth understanding of the issues under study. Mental health issues have great societal relevance but can end up “between chairs” due to their complexity and because they require knowledge from different areas or disciplines. The interdisciplinary group behind the research project consists of both researchers and clinicians, and they represent social science, medical and nursing perspectives, with professional backgrounds that include psychology and psychiatry, medicine, nursing and behavioral economics. Research shows that heterogeneous groups promote creativity since they can facilitate flexible idea generation, awareness of underlying connections between different ideas and access to more unconventional knowledge [35].

Overall, the research project will generate results that can provide a basis for decisions concerning further implementation and use of the PCBH model and has the potential to generate clinically meaningful results for the future development of mental health care provision in primary care. The project’s study design will make it possible to assess many important effects of the PCBH service delivery model at different levels (patient, staff and organization) and provide evidence of the effectiveness (or not) of the PCBH model under routine conditions in primary care.

## Data Availability

No datasets were generated or analysed during the current study.

## Abbreviations

ACG: Adjusted Clinical Groups
ATC: Anatomical Therapeutic Chemical
BHC: Behavioral Health Consultant
CBT: Cognitive Behavioral Therapy
CNI: Care Need Index
COPSOQ: Copenhagen Psychosocial Questionnaire
ICD: International Classification of Disease
ITT: Intention to Treat
KEDS: Karolinska exhaustion disorder scale
PCBH: Primary Care Behavioral Health
RQ: Research Questions
RÖ: Region Östergötland
